#### Assessment of the gut Lactococcus DNA and other microbial DNA

2.8.4

Fecal samples will be collected from all participant at each time point. Faecal DNA will be isolated using the same method as previously described for blood DNA isolation. YDB DNA from feces will be processed and analyzed using the same pipeline as for blood-derived DNA.

### Statistical analysis

2.9

The primary outcome is the change in relative abundance of blood YDB DNA across five time points. This will be analyzed using repeated measures ANOVA to detect statistically significant within-subject changes over time. The secondary outcomes include changes in all other non-human microbial DNA, which will also be analyzed using repeated measures ANOVA. All statistical tests will be two-tailed, with significance set at p < 0.05.

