### Study design

2.1

We will perform a within-subjects crossover trial with a single arm to study the effect of yogurt on the blood and fecal YDB levels in healthy volunteers. Participants will first undergo a 10-day period of dairy product withdrawal. Given that the half-life of bacterial DNA in blood is likely less than 24 h, a 10-day withdrawal period should be sufficient to substantially reduce circulating DNA fragments originating from *L. lactis*. Following the reintroduction of dairy (via yogurt consumption that is host to LGG, LA-5 and BB-12 cultures), we expect these specific bacteria and other YDB DNA to reappear in the bloodstream. While the precise kinetics of this reappearance are not yet known, our study is designed to detect these temporal changes and establish a foundation for understanding the dynamic relationship between dietary intake, the gut microbiome, and the blood microbiome.

This study is approved by the ethics committee of Erasmus Medical University Center Rotterdam in May 2025 (NL88008.078.24) and is registered at www.clinicaltrials.gov (NCT06944002), hence prior to participant's enrollment. This study will be conducted in accordance with the principles of the Declaration of Helsinki (75th WMA General Assembly, Helsinki, Finland, October 2024) and the Medical Research Involving Human Subjects Act (WMO). Interested volunteers will be provided with detailed information about the study and will give written informed consent prior to participation.

Participants will be studied at multiple time points using a within-subject crossover design (Fig. 1). At baseline, prior to any dietary intervention, blood and stool samples will be collected. Following this, participants will abstain from all dairy products for 10 days, after which a second set of blood and stool samples will be collected to confirm the expected disappearance of YDB DNA from both fecal and circulating microbial DNA pools.

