### Inclusion criteria

2.3

1)Age 18–65 years2)18.5 =< BMI <25 kg/m23)All genders included4)Not be lactose intolerant5)Willing to consume milk

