#### Primary objective

2.5.1

The primary objective is to examine yogurt-dependent bacterial (YDB) DNA counts in fecal and blood samples before and after dairy consumption. YDB, such as *Lactococcus lactis*, are transient residents of the human gut, only present following dairy intake, and therefore represent modifiable components of the intestinal microbiome. Detection of YDB DNA fragments in the bloodstream after dairy reintroduction will provide definitive evidence on the extent to which the blood microbiome reflects relevant changes in the intestinal microbiome. In this specific study, the use of a commercial yoghurt (but verified by independent agar growth testing) containing a defined consortium of bacteria adds signature species whose detection provides convincing signals in this respect.

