### Power analysis

2.6

This is a pilot study. This research has never been conducted before, making it difficult to determine a definite sample size. Based on published studies showing significant change in the relative abundance of gut microbiome at the phylum level upon consumption of fermented milk in 6 volunteers (Firmicutes and Bacteroidetes; p < 0.05 when comparing milk consumption vs. baseline) [20], and that the relative abundance of Bifidobacterium species increased following the consumption of human milk oligosaccharides by 7 volunteers over 7 days (p < 0.05 when comparing four type of milk concentrations with baseline) [21], we have chosen to include 10 volunteers for this study. If this is not sufficient to convincingly demonstrate trends of *Lactococcus lactis* DNA during 7 days of milk consumption intervention, then blood microbiome studies may not be powerful enough to show meaningful changes in intestinal microbiome composition.

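### The primary five-visit repeated-measures ANOVA does not isolate the question that decides the trial, whether blood YDB DNA rises from the end of withdrawal to after yogurt, and a withdrawal fall alone can make it significant

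*Protocol article*

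**What the plan says.** Section 2.9 (Statistical analysis) defines the endpoint: "The primary outcome is the change in relative abundance of blood YDB DNA across five time points". It then fixes the test: "This will be analyzed using repeated measures ANOVA to detect statistically significant within-subject changes over time". The level follows: "All statistical tests will be two-tailed, with significance set at p < 0.05". With 10 participants and five visits, the time effect has 4 and 36 degrees of freedom. No comparison between particular visits is named.

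The scientific question is narrower. Section 2.1 describes ten days without dairy, then yogurt, and says: "we expect these specific bacteria and other YDB DNA to reappear in the bloodstream". Section 2.5.1 says what would settle the matter: "Detection of YDB DNA fragments in the bloodstream after dairy reintroduction will provide definitive evidence".

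The five visits, in the labels of Table 1, are T-10 (before withdrawal), D0 (end of withdrawal), and D1, D2 and D7 (24 h, 48 h and one week after yogurt starts). Intake before T-10 is not standardised. Section 2.3 excludes lactose intolerance and asks for people "Willing to consume milk". Section 2.4 bars regular prebiotic or probiotic use but exempts yogurt and young soft cheese.

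On size, section 2.6 says "we have chosen to include 10 volunteers for this study" and gives no effect size, SD or power. It explains: "This research has never been conducted before, making it difficult to determine a definite sample size".

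**The concern.** An overall F test asks whether any of the five means differ. The claim that matters is that D1, D2 and D7 lie above D0. These are different hypotheses, and T-10 is where they part. The protocol itself predicts a fall from T-10 to D0. If that fall occurs and blood YDB DNA then stays low, the declared primary test can still be significant.

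Both outcomes will be interpreted. The Discussion says success could validate the blood technology. Section 2.6 says that failure to show a convincing trend in 10 people would suggest blood microbiome studies lack the power to show meaningful gut changes. A primary p-value that cannot separate a withdrawal fall from a reappearance supports neither reading well.

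**Working it through.** **Plan's own figure.** None can be reproduced: the 10 volunteers were chosen by analogy with earlier studies of 6 and 7 volunteers. What can be checked is how the stated test behaves at n = 10.

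**Step 1: normal data.** Inputs from the protocol: n = 10, five visits, two-sided 0.05. Assumptions: normal residuals with SD σ, sphericity, and a shift of d residual SDs. The order of visits is T-10, D0, D1, D2, D7.

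Omnibus noncentrality: λ = n Σ(μj − μ̄)²/σ².

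- Reappearance, means (d, 0, d, d, d): μ̄ = 0.8d, so the sum is 4(0.2d)² + (0.8d)² = 0.8d² and λ = 8d².
- Withdrawal fall only, means (d, 0, 0, 0, 0): μ̄ = 0.2d, so the sum is (0.8d)² + 4(0.2d)² = 0.8d² and λ = 8d².

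The noncentrality is identical, so the test rejects equally often whether or not anything reappears.

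Contrast, mean(D1, D2, D7) − D0: the variance is σ²(1/3 + 1)/10 = 0.133σ², the standard error 0.365σ and the noncentrality d/0.365 = 2.74d, on 9 df. Without reappearance its expectation is zero whatever happens at T-10.

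| d | λ | Omnibus, reappearance | Omnibus, withdrawal fall only | Contrast, reappearance | Contrast, withdrawal fall only |
|---|---|---|---|---|---|
| 0.5 | 2 | 16% | 16% | 23% | 5% |
| 1.0 | 8 | 54% | 54% | 68% | 5% |
| 1.5 | 18 | 91% | 91% | 95% | 5% |
| 2.0 | 32 | 99.5% | 99.5% | 99.8% | 5% |

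If T-10 is already as low as D0, means (0, 0, d, d, d): μ̄ = 0.6d, the sum is 2(0.6d)² + 3(0.4d)² = 1.2d² and λ = 12d². At d = 1 the omnibus test then has 74% power against 68% for the contrast.

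**Step 2: sparse, skewed counts.** Low values are plausible, because section 2.1 expects YDB DNA to disappear by D0 and section 2.8.1 describes very low microbial biomass. The distribution is not given, so everything here is assumed. The model is zero-inflated lognormal-Poisson: about 10 reads when present, background mean 0.3 reads, log-SD 1.0 within and 0.7 between participants, detection 10% at D0, 30–60% at T-10 and, with reappearance, 60–80% after yogurt.

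| Scenario | Omnibus, untransformed | Omnibus, log | Contrast, log |
|---|---|---|---|
| T-10 higher, no reappearance | about 6–34% | 12–63% | near nominal |
| Reappearance | about 13–23% | 40–82% | 68–94% |

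The ranges move somewhat with the settings: another run of this model gave 9–27%, 38–88% and 67–94% for reappearance. A rerun put the contrast's t test at about 7% without reappearance, slightly above 5%, which is a reason to prefer a permutation test.

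A second assumed model used overdispersed counts with a 10-fold return to the T-10 level. It gave 4–24% untransformed omnibus, 17–88% log omnibus and 54–98% log contrast. With a 20-to-1 withdrawal fall only, the untransformed omnibus test rejected 41–89% and the log contrast about 5%.

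**The case against.** The strongest reply is that the withdrawal fall is itself a predicted response. Section 2.1 collects D0 samples to confirm disappearance, and the Discussion states the aim as responsiveness to dietary change. On that view an overall test of change is relevant, and it does answer section 2.9's own wording. This stands in part: it would be too strong to say the primary p-value answers no stated question. But section 2.5.1 ties the definitive evidence to detection after reintroduction, and the overall test cannot show that.

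A reader might also infer that the plan analyses untransformed values, ignores sphericity and drops anyone with a missing sample. The article is silent on all three. They are commonly settled in an analysis plan that is not shown, so they are not findings here. None would repair the point: a transformed, sphericity-corrected omnibus test still includes T-10 and still has no direction.

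Nor do the documents support a flat claim that the ANOVA has little power. For roughly normal data and a shift of 1.25 to 1.5 residual SDs its power is 76–91%. On sparse counts, part of the gap between the untransformed omnibus test and the log contrast comes from the scale, not the contrast.

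Finally, eligibility does more than ask about willingness to consume milk. What remains true is that habitual yogurt intake before T-10 is permitted and not standardised.

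Pilot status excuses the absence of a power calculation. It does not excuse a primary test aimed at a broader question than the one to be interpreted.

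**Conclusion.** The point holds in a specific form: the stated primary test cannot distinguish a withdrawal fall from a reappearance after yogurt. That follows from the text and from the equal noncentrality, 8d² in both cases. Its size under normality and sphericity with n = 10 is 54% rejection at d = 1 and 91% at d = 1.5 with nothing reappearing, against 5% for the direct contrast.

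On sparse counts the same false attribution runs from about 6% to 63%, depending on T-10 detection (30–60%) and scale. Those figures, and the power comparison, rest on assumed count models and should be read as conditional. A reader might conclude that a true reappearance will probably be missed; the documents give no variance or effect size from which to say so. The mismatch should be corrected before the data are analysed.

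**What to change.** In section 2.9 and the analysis plan:

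1. Name as the primary analysis the within-participant contrast mean(D1, D2, D7) minus D0, on a log scale with a stated offset or in a count model. Use a small-sample test such as permutation of the D0, D1, D2 and D7 labels within participant, and report an estimate with a confidence interval.
2. Test T-10 versus D0 separately, as the secondary withdrawal effect.
3. Keep the five-visit ANOVA as supportive.

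The cost is wording; no samples, visits or participants are added. The statistical cost is a few points of power against a log-scale omnibus test in some cases where T-10 is as low as D0 (0.69 against 0.74 in one simulated case; 68% against 74% for normal data at d = 1).

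Averaging the three post-yogurt visits also dilutes a late rise, and section 2.1 says the kinetics are unknown. In simulated gradual-rise scenarios the log contrast had 45–72% power and the log omnibus test 37–78%, the latter helped by the T-10 difference. If a late rise is thought likely, the weighting of the visits should be fixed in advance.

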## Discussion

3

The existence of a common core blood microbiome in humans remains a subject of debate [10,13]. Most previous studies are cross-sectional and often lack rigorous controls for environmental contamination and database misclassification, which poses a significant challenge and hinders progress in the field. Another major limitation is the absence of longitudinal within-subject controls, which are essential for identifying and correcting potential false positives or negatives caused by individual variability and limitations in bioinformatics pipelines [14]. Furthermore, while the gut microbiome is frequently proposed as the primary source of blood microbial DNA, this hypothesis has not yet been definitively proven.

To overcome these challenges, a longitudinal design using a safe, well-characterized intervention that reliably alters the gut microbiome offers a promising solution. Yogurt, generally regarded as safe and nutritional beneficial, increase levels of beneficial bacteria such as *Lactococcus* and *Lactobacillus*, which are closely linked to immune function [40]. Given the established translocation of gut microbiome-derived metabolites, it is plausible that microbial DNA from yogurt-sensitive gut bacteria could also enter circulation and contribute to the composition of the core blood microbiome. In addition to its microbiome-modulating effects, yogurt provides essential vitamins and minerals such as riboflavin, zinc, selenium, and magnesium that support immune health as well. These combined advantages make yogurt a suitable, targeted and practical modulator for studying the presence and behavior of YDB DNA in circulation.

If cmDNA in blood correlates with the fecal microbiome, the use of defined probiotic strains in yogurt as spike-in controls may offer evidence supporting cm DNA as a valid representation of the colonic microbial composition of the participants involved. Importantly, while these introduced species primarily serve as a proof-of-principle to demonstrate detectability in blood, comprehensive microbiome profiling of fecal material will allow direct correlation analyses with respect to the amount of these bacteria in the volunteer intestine. Thus substantial insight into the relationship between gut and blood microbial signals is expected to be gained in this respect. Should proof-of-principle be established, a future dose response study will allow making more precise quantification and validation of these correlations.

By analyzing YDB DNA in both blood and fecal samples before and after yogurt reintroduction, this study aims to assess the responsiveness of the blood microbiome to dietary changes. If successful, the results could validate our blood microbiome technology and establish a foundation for non-invasive microbiome monitoring. These findings may offer important insights into host–microbiome interactions and contribute to the development of novel diagnostic tools for health monitoring and disease prevention.

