**Method/design:**

This study aims to establish or rule-out cmDNA as a representative of the gut microbiome. In a prospective, single-arm crossover trial, effects of dairy product withdrawal and reintroduction of a yoghurt with a known consortium of bacteria will be assessed in healthy volunteers aged 18–65. Participants will first abstain from all dairy products, a phase expected to reduce yogurt-associated cmDNA in the bloodstream. Yogurt will then be reintroduced, during which reappearance of cmDNA of specific bacteria (especially LGG, LA-5 and BB-12) is anticipated. Shotgun metagenomic sequencing will be used to track cmDNA dynamics over time. This longitudinal sampling approach will provide experimental evidence supporting the existence and responsiveness of the circulating microbiome, while also revalidating the bioinformatic pipeline used for its analysis.

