**Conclusion:**

This pilot study will test whether blood-derived microbial DNA can serve as a valid surrogate for gut microbiome composition. If successful, this approach may provide a more stable and integrative alternative to fecal sampling and support future biomarker development and mechanistic research.

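### The article promises to establish or rule out blood as a surrogate for the gut, but its stated tests assess only change over time and none links blood to stool within a participant

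*Protocol article*

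**What the plan says.** The declared question concerns the relation between two specimens. The Abstract (Method/design) says: "This study aims to establish or rule-out cmDNA as a representative of the gut microbiome". Its Conclusion says that the pilot will "test whether blood-derived microbial DNA can serve as a valid surrogate for gut microbiome composition". Section 2.5.1 treats detection in blood after dairy reintroduction as definitive on how far blood reflects intestinal change. Section 2.5.2 asks whether other microbial DNA in blood mirrors shifts in the gut.

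The stated tests concern time. Section 2.9: "The primary outcome is the change in relative abundance of blood YDB DNA across five time points", to be "analyzed using repeated measures ANOVA to detect statistically significant within-subject changes over time". Then: "The secondary outcomes include changes in all other non-human microbial DNA, which will also be analyzed using repeated measures ANOVA". Section 2.8.3 adds ANOSIM between time points and LEfSe for group-wise differences. Stool is covered as well: Table 2 lists the gut microbiome as a secondary outcome at all five visits, and section 2.8.4 sends stool through the same pipeline as blood.

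A blood-stool correlation appears only in section 3 (Discussion), which says that "comprehensive microbiome profiling of fecal material will allow direct correlation analyses with respect to the amount of these bacteria in the volunteer intestine".

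**The concern.** A significant time effect in blood shows that blood YDB (yogurt-dependent bacterial) DNA changed. A significant time effect in stool shows the same for stool. Two such results side by side show that both specimens responded to the diet. They do not show that one participant's blood level follows that participant's stool level, which a claim of representation or surrogacy needs. The Discussion makes correlation the condition for saying that blood represents the colonic composition of the participants, so the claim is at person level.

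The design also makes a correlation easy to misread. Section 2.1 expects YDB DNA to disappear from both specimens at the same visit and to reappear in blood after yogurt. A correlation computed across visits picks up that imposed pattern. With nothing fixed in advance, such a result could be reported as proof of surrogacy.

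**Working it through.** **1. Question against tests**

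| Place | Question or test | Relates a participant's blood to own stool? |
|---|---|---|
| Abstract, 2.5.1, 2.5.2 | Does blood represent, reflect or mirror the gut? | Needed |
| 2.9, primary | Repeated measures ANOVA, blood YDB over five visits | No |
| 2.9, secondary | Repeated measures ANOVA, other microbial DNA | No |
| 2.8.3 | ANOSIM between time points; LEfSe | No |
| 3 Discussion | Correlation, no method or unit given | Possibly |

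**2. Inputs from the article**

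- Participants: "we have chosen to include 10 volunteers for this study" (section 2.6). This number rests on analogy with published studies of 6 and 7 volunteers. No formula, effect size or power is given, so there is no figure to reproduce.
- Five visits, hence 10 × 5 = 50 blood-stool pairs.
- Error level: "All statistical tests will be two-tailed, with significance set at p < 0.05".

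**3. Assumptions (not in the article)**

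- Each specimen has total variance 1 within a visit. Intraclass correlation (ICC) is 0.3, 0.5 or 0.7.
- Person effects and residuals are independent between blood and stool, so the true person-level link is zero.
- Both specimens share the visit pattern present, absent, present, present, present, with withdrawal shift d in total-SD units.

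**4. Expected correlation with no person-level link**

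The variance of the pattern 1, 0, 1, 1, 1 is 0.8 × 0.2 = 0.16, so the variance of the visit means is V = 0.16 d². For d = 1.25, V = 0.16 × 1.5625 = 0.25, a visit-mean SD of 0.5.

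- All 50 pairs pooled: r ≈ V/(V + 1) = 0.25/1.25 = 0.20. The critical r at 48 df is 0.28.
- Person means removed: r ≈ V/(V + 0.8(1 − ICC)), which is 0.25/0.81 = 0.31, 0.25/0.65 = 0.38 and 0.25/0.49 = 0.51 at ICC 0.3, 0.5 and 0.7. The critical r at 39 df is 0.31.

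**5. Simulated rate of p < 0.05 (ICC 0.3 / 0.5 / 0.7)**

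| Analysis | d = 0 | d = 1.25 |
|---|---|---|
| 50 pairs pooled, 48 df | 9 / 16 / 26% | 33 / 37 / 42% |
| Person means removed, 39 df | about 5% | 52 / 74 / 97% |
| Person and visit means removed, 35 df | about 5% | about 5% |
| D0-to-D7 change across 10 people, 8 df | about 5% | about 5% |

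With d = 0 the excess in the pooled row arises only because 50 pairs from 10 people are treated as independent.

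The result depends on the shift. At d = 0.5 the pooled rates are 9 / 16 / 26%, no higher than with no shift. At d = 2 (ICC 0.3 and 0.5) they are 86% and 84%, and 98% and 99.9% with person means removed.

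**6. What ten participants can show**

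With a true residual correlation of 0.3, 0.5 or 0.7 (ICC 0.5), power is 45%, 90% and 99.9% after removing person and visit means, and 14%, 33% and 68% for the change correlation. The change correlation must exceed 0.63 to reach p < 0.05. These figures assume equal variance at every visit.

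**The case against.** The case on the other side has four parts.

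- **Stool is analysed.** A reader might infer that only blood is tested over time. The article does not support that: section 2.9 covers all other non-human microbial DNA, and Table 2 and sections 2.8.3 and 2.8.4 bring in stool. What is absent is a test joining the two specimens.
- **No faulty correlation is specified.** A reader might infer that the correlation in the Discussion pools 50 pairs and will come out positive whatever the truth. The article does not say so. A correlation at a single visit does not carry the visit pattern, and one of individual changes keeps its 5% level. Even when pooled, most simulated trials at a 1.25 SD shift are not significant. The inflation is a risk left open, not a planned error. The details may sit in a fuller document, and their absence alone is no finding.
- **The joint fall and return is real evidence.** It is the effect that the intervention is meant to produce, and the Discussion names responsiveness to diet as an aim. Removing visit means removes this signal, so it must keep a place in the conclusions.
- **The study is a pilot.** The Discussion says that correlation may offer evidence, and leaves quantification and validation to a later study.

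All four stand, and they limit the point. They do not remove the mismatch: the article fixes its primary and secondary tests, and those tests answer a different question from the one in the Abstract and section 2.5.1.

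**Conclusion.** The concern holds in a limited form. The stated tests can show that YDB DNA in blood, and in stool, changes with the diet. They cannot establish or rule out that blood represents or stands in for a participant's gut microbiome, and detection in blood is not definitive on that question. This conclusion comes from the text and needs no assumption.

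The numerical part is conditional. It requires a correlation taken across visits that ignores participant, visit or both, and it rests on assumed ICCs of 0.3-0.7 and an assumed shared shift. The article expects disappearance and return, so a sizeable shift is its own planned scenario, but it gives no size.

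**What to change.** Add to section 2.9 one named blood-stool analysis, in either form:

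- Regress blood YDB on stool YDB from the same visit, both on a log or log-ratio scale, with visit as a factor. Split stool into its participant mean and the deviation from that mean. The first slope asks whether people with more in stool have more in blood; the second asks whether blood follows stool within a person. If only the second is wanted, fit participant as a fixed effect. A participant random effect with unsplit stool would blend the two slopes.
- Correlate individual D0-to-D7 changes in blood and stool across participants.

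Report the estimate with its 95% CI. Report the joint fall and return of the visit means separately, as evidence of responsiveness. Base any statement about person-level representation or surrogacy on the paired analysis. Otherwise reword the Abstract's Conclusion and section 2.5.1 so that they claim only responsiveness of blood YDB DNA to yogurt.

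The cost is about a paragraph of text and a little more analysis, since Table 1 already schedules both specimens at all five visits. The drawbacks are imprecise estimates with ten participants and a conclusion that may be less favourable. D0 will also add little within-visit information if stool YDB is near zero then. That is likely, because section 2.7.2 uses stool YDB as one check on withdrawal and replaces participants judged not withdrawn.
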